### Recruitment

Recruitment of participants will be done through routine NUHDSS rounds whereby pregnancy registration is done for female residents aged 12 to 49 years in each household. This will be complemented by other means of identification of pregnant women including through antenatal care providers in the study areas and use of community informants to ensure high coverage. All known pregnant women in the two study slums that fall within the Nairobi Urban Health and Demographic Surveillance Area will be invited to be recruited to the study until the desired sample size is achieved. Recruitment is expected to be for a period of approximately one year and three months from September 2012 to December 2013.

### Sample size considerations

The sample size determination was done considering the study design of cluster randomisation since villages in the study sites will be randomised to either control or intervention [29]. A minimum sample size for both intervention and control arms of 196 was estimated to have enough power to detect an increase in exclusive breastfeeding for six months from two per cent (the baseline rate of exclusive breastfeeding in the study setting) [22] to 12%; a ten percentage point increase, although higher increase has been documented in similar interventions elsewhere in the developing world [30]. We used a level of precision of five per cent (for a two-sided *t*-test) and power of 80%. We then adjusted for expected intra-cluster correlation (ICC) using a design effect of 3.2. The design effect was based on an ICC of 0.05, based on previous research on breastfeeding practices in the study area which acts as a baseline for the current study. We allowed for 20% potential attrition, also based on previous research in the study area [31]. Therefore, an effective sample size of about 780 mother-child pairs was estimated. We used practice of exclusive breastfeeding to undertake the sample size calculations as it is our primary outcome of interest. (More detailed account of sample size determination is attached as an additional material in Additional file 1).

### Intervention

The intervention will involve personalised, home-based counselling of pregnant women and mothers of infants on optimal MIYCN practices by CHWs Table 1.

**Table 1 T1:** Intervention versus control group

**Intervention group**	**Control group**
A) Personalised, home-based counselling of mothers on maternal, infant and young child nutrition (MIYCN) (intervention)	A) **Not Provided**
B) Distribution of MIYCN educational materials (usual care)	B) Distribution of MIYCN educational materials (usual care)
C) Home-based counselling by community health workers (CHWs) on usual care (for example, ante-natal care, delivery with skilled attendants, immunization)	C) Home-based counselling by CHWs on usual care (for example, ante-natal care, delivery with skilled attendants, immunization)

A formative study will be conducted before the roll-out of the intervention to inform the design and components of the intervention including content of the counselling messages. This will involve a qualitative study involving interviews with key informants in the study communities including community leaders, CHWs, traditional birth attendants (TBAs) and health professionals; mothers (pregnant, breastfeeding and mothers of children under five years. Additionally, consultations will be held with key organizations including the Division of Nutrition and the Division of Community Health Services in the Ministry of Health; UNICEF and other organization working on MIYCN issues. The information gathered will be used to adapt the counselling messages and information materials. The formative study will also establish mechanisms for successfully engaging CHWs into the study. More details on data collection are given below.

Existing CHWs within the Government’s Community Strategy in the study area will be trained on counselling of appropriate MIYCN practices using The Community Infant and Young Child Feeding (IYCF) Counselling Package developed by UNICEF in partnership with other organizations, which has been adopted by the Kenya Ministry of Health (http://www.unicef.org/nutrition/files/Facilitator_Guide_September_2011_clean.pdf).

The elements of counselling package are based on WHO/UNICEF IYCF guidance documents, training and other materials, including the Infant and Young child feeding counselling integrated course [32]. The package is designed to equip community workers or primary health care staff to be able to support mothers, fathers and other caregivers to optimally feed their infants and young children. The CHWs will be equipped with infant and young child feeding counselling cards; brightly coloured illustrations that depict key infant and young child feeding concepts and behaviours for the CHWs to share with mothers, fathers and other caregivers. The package will be adapted to include counselling messages on maternal nutrition.

Counselling will be initiated during pregnancy as soon as the mother is recruited and will be continued until the end of infancy (one year after delivery). Counselling will encompass maternal nutrition, immediate initiation of breastfeeding after birth, breast positioning and attachment, exclusive breastfeeding, frequency and duration of breastfeeding, expressing breast milk, storage and handling of expressing and lactation management. It will also focus on age-appropriate complementary feeding, starting at six months: age appropriate complementary foods (nutritious, safe, affordable, and locally available), feeding frequency and quantity, and appropriate feeding practices including hygiene and responsive feeding behaviours, which encourage mother-child interaction during feeding [33,34]. For the intervention arm, CHWs will visit the pregnant woman about once every month up to week 34, after which they will visit the mother weekly until delivery. After delivery, they will visit the mother weekly in the first one month, then once a month until the end of infancy, but during the fifth month when mothers are expected to initiate complementary feeding, the frequency will be biweekly.

All recruited pregnant women in both the intervention arm and control arm will receive information materials regarding MIYCN throughout the follow-up period; these are normally provided by the Ministry of Health for distribution as part of the standard care. Additionally, the recruits will be provided with standard care counselling by CHWs, which will address antenatal and postnatal care, appropriate tests during pregnancy, health facility delivery, general nutrition, hygiene, and immunization. Women in the control arm will be visited according to the usual practice within the Community Strategy whereby they visit households according to the needs of the household.

Though we will not seek to establish HIV status of the participants, mothers in the intervention arms will be advised on how they should feed the child in case a mother is HIV positive, while the information materials given to both intervention and control arms will also stipulate information on feeding for HIV-exposed infants. Rigorous monitoring of the intervention will be done to ensure that the CHWs deliver the intervention as required. This monitoring will be done by an Intervention Monitor assisted by field assistants using monitoring tools developed for the project including mother’s diary and CHWs reporting tools. The CHWs will be expected to submit weekly reports of their activities to the intervention monitor. Additionally, close supervision of the activities of the CHWs will be done through regular spot checks and sit-in sessions by the intervention monitor. Further, a midline qualitative process evaluation will be done to assess if the intervention is happening as planned and assess areas that need improvement. The qualitative study will involve in-depth interviews and focus group discussion with mothers and CHWs.

### Assessment

#### *Outcome measures*

##### 

**Primary outcomes** The primary outcome measure is exclusive breastfeeding for six months.

This will involve determining the change in the rate of exclusive breastfeeding for the first six months. Mothers will be advised on what they need to do with regard to breastfeeding and how they should do it, including breast positioning and attachment and expressing and storing breast milk. This advice is expected to lead to self-efficacy with regard to breastfeeding, hence adherence to WHO guidelines on breastfeeding, resulting in improved rates of exclusive breastfeeding for six months. Data on breastfeeding practices will be collected longitudinally from birth every two months through an interviewer-administered questionnaire to the mother. Self-reported exclusive breastfeeding will be validated on a 10% sample using the stable isotope technique (dose-to-the mother of deuterium oxide) for breast milk analysis. The 10% sample will be randomly selected from the list of participating breastfeeding mothers. The procedure will be carried out once per mother-child pair, sampled before the child is aged six months.

##### 

**Secondary outcomes** Secondary outcomes include:

1. Breastfeeding and complementary feeding knowledge and attitudes according to WHO recommendations [9]. Data will be collected every two months following recruitment through an interviewer-administered questionnaire to the mother to determine change in knowledge, attitudes and practice with the intervention.

2. The duration of any breastfeeding in months.

This will include duration of any breastfeeding in months. Data will be collected longitudinally every two months following birth through an interviewer-administered questionnaire to the mother to determine if the child is still breastfeeding, and if so, whether they have started feeding on other foods/fluids other than breast milk; when they started on other foods/fluids; and if they stopped breastfeeding, when they stopped.

3. Complementary feeding practices.

This will focus on complementary feeding practices with regard to WHO recommendations, including timing of introduction of solid, semi-solid or soft foods; minimum dietary diversity; minimum meal frequency; minimum acceptable diet and consumption of iron-rich or iron-fortified foods [http://www.who.int/nutrition/publications/infantfeeding/9789241599290/en/] [9]. Data will be collected longitudinally every two months following birth through an interviewer-administered questionnaire to the mother to determine if the child has started feeding on foods/fluids other than breast milk and when they started, frequency of feeding, type of foods/fluids including dietary diversity through 24-hour recall, hygiene practices, and responsive feeding behaviours.

4. Nutritional status as determined by stunting, underweight, and wasting.

Interventions aimed at promoting optimal breastfeeding and complementary feeding practices have been found to reduce malnutrition among infants and young children [35]. It is therefore expected that the proposed intervention will have an effect on the levels of stunting, underweight and wasting. Anthropometric measurements: weight, length/height and mid-upper arm circumference will be collected on the child every two months during the follow-up period. All anthropometric measurements will be carried out according to standard procedures [36]. For determination of underweight, stunting, and wasting, weight-for-age z-scores (WAZ), height-for-age z-scores (HAZ) and weight-for-height z-scores (WHZ), respectively, will be generated using the World Health Organization (WHO) 2006 growth standards [37]. Stunting will be determined as HAZ < -2, underweight as WAZ < -2 and wasting as WHZ < -2 [38].

5. Morbidity from diarrhea.

Evidence indicates that breastfeeding is preventive against infections such as rotaviral diarrhoea [39]. It is therefore expected that promotion of exclusive breastfeeding would impact the rate of diarrhoea morbidity. Data on diarrhea morbidity in the last two weeks for the child will be collected longitudinally through an interviewer administered questionnaire to the mother every two months during the follow-up period.

6. Cost-effectiveness. Data on the cost of implementing the intervention from the provider perspective will be obtained from the project’s administrative records at the end of the study. By combining the cost and the effectiveness data, we will calculate the average cost-effectiveness ratio and the incremental cost effectiveness ratio.

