### Statistical analysis

Determination of change for the primary outcome (exclusive breastfeeding) will be done at month six. Difference in duration of exclusive breastfeeding will also be determined longitudinally up to six months between the intervention and control groups. Comparison for other outcomes such as morbidity from diarrhea and malnutrition will be done longitudinally at around month three, six, nine and twelve. Analyses will involve a comparison of differences in the intervention and control groups with regard to the primary outcome (exclusive breastfeeding) and secondary outcomes (other infant feeding practices, diarrhea morbidity and nutritional outcomes), controlling for baseline measures (for example, previous breastfeeding practices) and prognostic factors (for example, Socio-economic status (SES) and household food security) if randomization of the clusters does not control for differences in these factors at baseline. Statistical methods to determine change will include analysis of covariance (ANCOVA) for continuous variables (for example, duration of exclusive breastfeeding and any breastfeeding and multinomial logistic regression analysis for categorical variables (that is, whether exclusively breastfed for six months or not) [40]. Additionally, survival analysis (proportional hazard analysis) for variables measured longitudinally (for example, duration of breastfeeding and malnutrition and multilevel modelling for repeated measures such as diarrheal morbidity will be applied. Intention-to-treat analysis [41] will be applied as appropriate. Efforts will be made to maximize follow-up of participants, using the NUHDSS framework to minimize missing information. Quantitative data analysis will mostly be done using Stata version 12.1. (StataCorp LP, College Station, Texas, USA). (See Table 2 for detailed outline of data analysis plan).

**Table 2 T2:** Data analysis outline

**Study objective**	**Outcome variables**	**Independent variable**	**Control variables**	**Type of analysis**
1. To determine the effect of the intervention on breastfeeding and complementary feeding knowledge, attitudes and practices among mothers of infants	1. Knowledge and attitude levels on breastfeeding and other infant feeding practices	Intervention status	SES^1^, food security, maternal demographic characteristics, antenatal care child morbidity	Multinomial logistic regression for rates and survival analysis for duration

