	2. Breastfeeding practices, including initiation of breastfeeding within one hour of birth, exclusive breastfeeding (for first 6 months) and duration of exclusive and any breastfeeding			
	3. Complementary feeding practices for example, optimal timing of initiation of complementary feeding and minimum dietary diversity, minimum meal frequency, and minimum acceptable diet			
2. To determine the effect of the intervention on nutritional outcomes among infants;	1. Stunting	Intervention status	SES, food security, maternal demographic characteristics, child morbidity, antenatal care, vaccination status	Multinomial logistic regression
	2. Underweight			
	3. Wasting			
3. To determine the effect of the intervention on morbidity from diarrhoea among infants	Diarrhoea morbidity	Intervention status	SES, food security, maternal demographic characteristics, child morbidity, antenatal care, vaccination status	Multilevel modeling
4. To determine the experiences, facilitating and limiting factors associated with the intervention	1. Client satisfaction	Not applicable	Not applicable	Descriptive (Outcome 1) Qualitative-thematic analysis (outcomes 2 and 3)
	2. Experiences			
	3. Limiting and enabling factors			
5. To assess the cost-effectiveness of the intervention	Cost-effectiveness	Not applicable	Not applicable	Cost-Effective Analysis

^1^SES=Socio-economic status.

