Other than just assessing the effectiveness of the interventions on breastfeeding and other infant feeding practices, this study will also determine the effectiveness of the intervention on other outcomes including morbidity from diarrhea and nutritional outcomes [48,49,52]. Studies elsewhere have indicated the effectiveness of interventions aimed at promoting breastfeeding on these outcomes. A good example of a study where these effects have been studied is the PROBIT (Promotion of Breastfeeding Intervention Trial) study in Belarus in 1996 to 1997 that involved slightly over 17,000 mother-child pairs. That study showed a significant reduction in the risk of gastrointestinal infections and a positive effect on growth of infants. The prevalence of gastro-intestinal infections was 9% in the intervention group compared to 13% in the control group (OR = 0.6; CI: 0.40-0.91; *P* <0.05). Likewise, infants in the intervention group were 106 g and 89 g heavier; and 0.50 and 0.46 cm taller at three and six months respectively compared to children in the control group (*P* <0.05) [49,52]. The effects may be related to optimal breastfeeding and other infant feeding practices on growth and morbidity.

Some limitations to this study may include bias in reporting of the primary outcome (exclusive breastfeeding). To counter this, objective breast milk analysis using the stable isotope technique will be used. It is possible that even with randomization of clusters, there will be difference in the baseline measures in the intervention and control group by chance. Analysis methods to be adopted will control for baseline differences. Additionally, given high mobility in the urban slums, some of the participants may be lost to follow-up, while some may also move to alternative group clusters. To counter this, intention to treat analysis will be adopted, while an allowance for loss to follow-up has been included in the sample size determination.

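### Growth is listed for analysis only as z-scores below -2; adding the mean z-scores already being generated would recover some precision at almost no cost

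*Protocol article*

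**What the plan says.** Under Outcome measures, secondary outcome 4 is named "Nutritional status as determined by stunting, underweight, and wasting". The three z-scores "will be generated using the World Health Organization (WHO) 2006 growth standards" in order to classify each child, and the classification is then fixed: "Stunting will be determined as HAZ < -2, underweight as WAZ < -2 and wasting as WHZ < -2". The schedule is frequent. Weight, length or height and "mid-upper arm circumference will be collected on the child every two months during the follow-up period".

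In Table 2 (Statistical analysis), objective 2 has three outcome variables, namely stunting, underweight and wasting, with "Multinomial logistic regression" as the analysis. The text of that section adds "survival analysis (proportional hazard analysis) for variables measured longitudinally (for example, duration of breastfeeding and malnutrition", which still starts from the binary status. It also provides "analysis of covariance (ANCOVA) for continuous variables", but the examples it names are breastfeeding durations. No section names a mean z-score as an analysed outcome.

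The Discussion supports the expectation of a growth effect with a large breastfeeding-promotion trial in which "infants in the intervention group were 106 g and 89 g heavier" at three and six months, with a corresponding difference in length.

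**The concern.** A child at -1.9 and a child at +1 count the same under the cut-off, and so do a child at -2.1 and one at -4. If counselling moves the whole distribution slightly, which is the kind of effect the Discussion cites in figures, an indicator at -2 sees only the children who cross that point. The z-scores will exist for every child and visit, yet as listed they serve only to form the indicators.

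The effect on nutritional outcomes is aim (ii) of the trial, and 14 clusters leave little precision to spare. Mean z-scores that are analysed but not named in advance would also look like an unplanned addition to the published outcomes.

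**Working it through.** **1. The plan's own figure.** The article gives no sample size, power or effect size for growth, so the primary-outcome calculation supplies the design inputs. For 2% against 12%, two-sided 5%, 80% power, unpooled variance: (1.960 + 0.842)² × (0.02×0.98 + 0.12×0.88) / 0.10² = 98.3 per arm, 196.5 in total (stated: 196). Then 196 × 3.2 = 627, and 627 / 0.8 = 784 (stated: about 780). The figure reproduces. The design effect of 3.2 corresponds to 1 + (45 - 1) × 0.05, that is, 45 analysed children in each of 14 clusters (14 × 45 = 630).

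**2. Inputs for growth.**
- From the article: 14 clusters; 627 analysed (313.5 per arm); stunting in about four in ten under-fives in the study slums (Background).
- Assumed: prevalences of 20% and 10%; an ICC of 0.05 for z-scores (the article's 0.05 is for breastfeeding practices); normal z-scores with equal SD; a pure location shift; one time point; a shift of 0.25 SD for the power figures.

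**3. Loss for independent children.** The efficiency of the indicator relative to the mean is E = φ(z_p)² / [p(1 - p)].
- p = 0.40: 0.3863² / 0.24 = 0.622, loss 38%
- p = 0.20: 0.2800² / 0.16 = 0.490, loss 51%
- p = 0.10: 0.1755² / 0.09 = 0.342, loss 66%

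**4. Loss in this clustered design.** Dichotomising weakens the correlation within clusters as well as the signal. If z-scores have ICC 0.05, the binary ICC is [Φ₂(z_p, z_p; 0.05) - p²] / [p(1 - p)], where Φ₂ is the bivariate normal distribution function. The binary design effect is 1 + 44 × that ICC, and the relative efficiency is E × 3.2 / (binary design effect).

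| Prevalence | Binary ICC | Design effect | Relative efficiency | Loss |
|---|---|---|---|---|
| 40% | 0.031 | 2.37 | 0.622 × 3.2 / 2.37 = 0.84 | 16% |
| 20% | 0.025 | 2.10 | 0.490 × 3.2 / 2.10 = 0.75 | 25% |
| 10% | 0.018 | 1.78 | 0.342 × 3.2 / 1.78 = 0.61 | 39% |

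**5. Power for an assumed 0.25 SD shift (normal approximation).**
- Mean z-score: effective n per arm = 313.5 / 3.2 = 98; Φ(0.25 / √(2/98) - 1.96) = Φ(-0.21) = 42%.
- Indicator, 40% falling to 30.7%: effective n = 313.5 / 2.37 = 132; Φ(0.0926 / 0.0586 - 1.96) = 35%.
- Indicator, 20% falling to 13.7%: effective n = 149; power 30%.
- Indicator, 10% falling to 6.3%: effective n = 176; power 25%.

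A simulation of 14 clusters of 45 with a cluster-level t-test (12 df) gives slightly lower values in the same order: about 36% for the mean against about 31-32%, 28% and 22-23%. If the shift were 0.15 SD, power on the mean would be only about 18%.

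**The case against.** The strongest reply is that this is a choice and not a mistake. The article expects an effect on the levels of stunting, underweight and wasting; the outcome, its definitions and Table 2 all match that expectation, and the economic evaluation counts malnutrition cases averted. A mean z-score answers a different question. This stands. It is why the indicators must stay and why nothing here is wrong or contradictory. A reader might infer that they should be demoted to supporting status, but the documents give no ground for that.

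A reader might also take 38% to 66% as this trial's loss. That range holds for independent children. Carrying it into the trial by applying 3.2 to both scales gives indicator power of about 27%, 22% and 16%, but z-scores with ICC 0.05 do not keep that ICC once they are cut.

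A third inference is that the cut-off would hide an effect the mean would otherwise find. At 42% power the mean itself misses a 0.25 SD shift more often than not. The main weakness is the number of clusters. The article gives no SD with which to turn the quoted gram differences into z-score units, so the assumed shift cannot be tied to them.

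Two further points stand in part. The provision for continuous variables is open-ended, and an analysis plan that is not shown could already include mean z-scores, so the word only refers to what the article lists. Proportional hazards for malnutrition also uses timing, so the single-time loss does not carry over exactly to that analysis.

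**Conclusion.** The point holds as a modest gain in efficiency. As listed, every growth analysis rests on a cut at -2, although the underlying z-scores are generated. Under the assumptions above, the cut costs about 16% of the information at 40% prevalence, 25% at 20% and 39% at 10%. The gap in power for a 0.25 SD shift is about 7, 12 and 17 percentage points.

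Only the 40% prevalence comes from the article, and it describes stunting in under-fives, whereas this trial follows infants to one year. No local prevalence of underweight or wasting is given, and the loss would be larger for an indicator rarer than 10%. The growth ICC, the shift, normality and the single time point are assumptions. The direction, less information from the indicator, is the same at all three prevalences examined, with or without clustering.

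The point concerns a secondary outcome. It does not touch the exclusive-breastfeeding analysis or the sample size.

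**What to change.** Add mean HAZ, WAZ and WHZ to objective 2 in Table 2 as prespecified comparisons. Analyse each with a linear mixed model with random effects for community unit and for child, estimating the difference between arms at the planned comparison times. Keep stunting, underweight and wasting alongside them, since the stated hypothesis and the economic evaluation need them. State the addition before the growth data are analysed by arm.

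The cost is one more model per index and a stated rule for handling implausible z-scores. No new measurements or participants are needed.
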